#### Treatment attitudes

Valuations for each of the two treatment options are asked on a 10-point scale ranging from 1 (very bad) to 10 (excellent). Satisfaction with the received treatment and with the physical and emotional effect of treatment is measured on a 6-point scale from 1 (dissatisfied) to 6 (very satisfied). Patient's attitudes towards striving for length (quantity) or quality of life are assessed with 8 items by the 'QQ Questionnaire' [29]. High scores on the quantity or quality scale indicate the importance of length and quality of life, respectively.

#### Substitute judgment

When the medical oncologist informs patients about this study, he or she is asked to judge whether or not the patient will desire information about adverse events, tumour response, and median survival that will be offered in the interview.

### Sample size calculation

Our primary research question is whether or not patients want to be informed. For study question 1a, about 100 patients in the intervention group will suffice to estimate an assumed desire rate for prognostic information of 80% with 95% confidence interval from 71% to 87%. For study question 1b, regarding factors that determine information desire, again about 100 patients will suffice to detect a weak correlation of 0.28 between a predictor and information desire, with α = 0.05 and a power equal to 0.82. For question 2, dealing with the ability of the medical oncologist to judge whether or not the patient wants this information, the same analysis applies as for study question 1b. For study question 3, which addresses the effect of the introduction of decision support compared to usual care on patient well-being, the intervention group is compared to the usual care group. Because one of the main concerns of physicians is that information on prognosis provokes anxiety, anxiety is used as the main outcome measure. We assume that the HADS anxiety difference between the two groups at t3 is equal to 2.2, and the correlation between the measurements at t1 and t3 equals 0.72. The standard deviation in each cell is about 6, corresponding to a medium sized effect size of 0.36. With α = 0.05, and 70 patients in each group, the power to detect the assumed effect is equal to 0.81. In conclusion, 100 patients in the intervention group and 70 patients in the usual care group suffice to answer the above research questions. Assuming that 30% of the patients refuse to give informed consent, and that 1% of patients has died at t3, 246 patients will have to be approached.

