**Methods/Design:**

This study is a randomized controlled trial of patients with advanced colorectal, breast, or ovarian cancer who have started treatment with first-line palliative chemotherapy. The trial will consist of 100 patients in the decision aid group and 70 patients in the usual care group. To collect complete data of 170 patients, 246 patients will be approached for the study. Patients will complete a baseline questionnaire on sociodemographic data, well-being measures, and psychological measures, believed to predict information desire. The medical oncologist will judge the patient's information desire. After disease progression is diagnosed, the medical oncologist offers the choice between second-line palliative chemotherapy plus best supportive care (BSC) and BSC alone. Randomization will take place to determine whether patients will receive usual care (n = 70) or usual care and the decision aid (n = 100). The aid offers information about the potential risks and benefits of both treatment options, in terms of adverse events, tumour response, and survival. Patients decide for each item whether they desire the information or not. Two follow-up questionnaires will evaluate the effect of the decision aid.

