### Procedure

The medical oncologist, or a nurse who first consulted the medical oncologist, will inform eligible patients in a general way that this study focuses on 'how to involve the opinion of patients in the treatment'. Next, he or she will ask whether the researcher can contact the patient by phone about this study. The oncologist or nurse is instructed not to discuss that survival information can be provided in the study, in order not to lose patients not desiring such information. After the visit of the patient, the oncologist fills in the medical history on the inclusion form. He or she also makes a judgment whether or not the patient will desire information about adverse events, tumour response, and median survival that will be offered in the interview (research question 2). In the phone call, patients are explained that data are collected by means of three questionnaires and possibly an interview. All patients who agree to participate will provide written informed consent.

Patients will be sent a baseline questionnaire (t1) to collect sociodemographic data, well-being measures, and measures that predict information desire. When tumour progression is diagnosed, second-line chemotherapy will be offered by the oncologist and randomization will be performed. Patients in the usual care group will receive information about the treatment choice from their oncologist. In the intervention group, patients will receive the same information, and will in addition be offered information in an interview using a decision aid. At the moment of disease progression, the medical oncologist is asked to estimate patient survival, because this is expected to be associated with the patient's information desire.

To evaluate the effect of the decision aid, two follow-up questionnaires will be sent to the patients, one week (t2) and eight weeks (t3) after the treatment choice, before the first evaluation of chemotherapy. Figure 1 displays the complete procedure.

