#### Sociodemographic variables and medical history

Self-report data are collected at t1 on demographic variables (age, marital status, having (grand)children, being religious, working status, and education) and on previous chemotherapy, including experienced benefits and adverse events, and time since last chemotherapy. Tumour and treatment characteristics such as primary tumour site, previous chemotherapy, and time since diagnosis are filled in on the inclusion form by the medical oncologist. At the moment of disease progression, the medical oncologist is asked to estimate patient survival. Answer possibilities are 3-6 months, 6-9 months, 9-12 months, and more than 12 months.

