## Discussion

This study attempts to settle the debate on the desirability of informing patients with cancer. To this end, the amount of information desired by patients with advanced cancer is investigated by offering information in a decision aid. Furthermore, the study will show whether it is possible to predict the amount of information desired, either by patient and disease-related factors, or by judgment of the medical oncologist. Concerns that the information may provoke patient anxiety are addressed by evaluating the effects of the decision aid using a randomized controlled design.

The study design has some limitations. Selection bias could be introduced when oncologists select patients who are more open to information or are in a better psychological state. When the data collection is completed, the role of selection bias can be investigated by comparing the resulting sample to other study samples, and comparing patient characteristics between physicians that included few versus many patients. Selective patient participation based on patients' information desire is addressed by informing eligible patients about the study in a general way, not mentioning the provision of (prognostic) information.

Patients have to fill in a baseline questionnaire that includes predictors for information desire and a baseline measurement for the effect of the information. Therefore, it is not feasible to include patients at the moment of the treatment choice; patients have to be included during first-line chemotherapy. This timing may positively affect the inclusion rate, since patients will be less distressed during first-line chemotherapy than at the moment of disease progression. On the other hand, due to the interval between the baseline questionnaire and the interview, the association between information desire and predictors may be weakened. In addition, the correlation between the effect measures at baseline (t1) and follow-up (t2 and t3) may be weakened.

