Randomization is, for practical reasons, performed by using sealed envelopes. In some of the 11 participating hospitals, there will be little time between the diagnosis of disease progression and subsequent consultation with a nurse. Therefore, instant randomization will be required and envelopes are a very practical method to perform this. The use of envelopes leaves a possibility to subvert the randomization procedure. However, a plain attempt to allocate a patient out of sequence will be discovered because the envelopes are sequentially numbered and the allocation can be compared with the predetermined sequence. The oncologist could also decide not to randomize a patient, but this would not go unnoticed since all patients are registered on the trial before the moment of randomization, therefore we will be able to compare patients who were and were not randomized.

Blinding of the medical oncologists and the patients is not feasible in this type of research, because patients may want to discuss the information from the decision aid with their oncologist. However, patients are blinded to the intervention in that they are not aware of the exact content of the decision aid; they are only informed that a new method of information giving is investigated.

A major strength of this study is that, in contrast to many previous studies, we will actually deliver information on treatment options to patients at the point of decision making. The results of this study can be applied to improve the provision of information in daily clinical practice. Generalization to the target population is facilitated by the broad inclusion criteria that are used in this study and the use of the decision aid by various nurses in the 11 participating hospitals. Furthermore, the method used to assess patients' information desire very much resembles information giving in clinical practice, by actually providing information at the moment of the treatment choice.

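### The 246 to be approached leaves about two patients to lose between consent and t3, with no term for consented patients never randomized or for unreturned t3 questionnaires

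*Protocol article*

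**What the plan says.** The Sample size calculation concludes that "100 patients in the intervention group and 70 patients in the usual care group suffice to answer the above research questions". It then allows for refusal and death only: "Assuming that 30% of the patients refuse to give informed consent, and that 1% of patients has died at t3, 246 patients" have to be approached. The Abstract (Methods/Design) attaches that figure to complete data: "To collect complete data of 170 patients, 246 patients will be approached for the study".

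On timing, the Discussion says that "patients have to be included during first-line chemotherapy". Under Procedure and Randomization, allocation happens only once progression has been diagnosed and second-line chemotherapy is offered. The follow-up questionnaires are sent "one week (t2) and eight weeks (t3) after the treatment choice, before the first evaluation of chemotherapy". The Discussion, writing about envelopes and about oncologists who might choose not to randomize, says that "we will be able to compare patients who were and were not randomized", because everyone is registered beforehand.

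At progression the oncologist estimates survival. The section on sociodemographic variables and medical history gives the scale: "Answer possibilities are 3-6 months, 6-9 months, 9-12 months, and more than 12 months".

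**The concern.** The recruitment figure must carry patients through four steps: consent, progression with an offer of second-line treatment and randomization, survival to t3, and return of the t3 questionnaire. The sum covers the first and third. A consented patient who dies, deteriorates or is not offered second-line treatment before progression is handled never enters either arm. Questionnaires sent by post or handed out are not all returned. Both losses are set to zero.

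The 1% for death also looks low for patients whose first-line palliative treatment has failed and whose expected survival is recorded in three-month steps starting at 3-6 months.

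If 246 is treated as the stopping point for recruitment, the trial may end with fewer than 100 interviews for the primary questions on information desire and fewer than 170 patients for the anxiety comparison. Patients missing at t3 through death or deterioration are also likely to be the sickest.

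**Working it through.** **Inputs from the article.** Refusal 30%; dead at t3 1%; target 170 = 100 + 70; t3 at 8 weeks (8/52 × 12 = 1.85 months); HADS anxiety difference 2.2; SD 6; t1-t3 correlation 0.72; α = 0.05 (taken as two-sided); stated power 0.81 with 70 per group; correlation 0.28 for question 1b with stated power 0.82.

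**Reproducing the plan.**
- 170/(0.70 × 0.99) = 245.3, rounded up to 246. This matches.
- 246 × 0.70 = 172.2 consenting, and 172.2 − 170 = 2.2 patients to spare. The 1% uses up most of it: 172.2 × 0.99 = 170.5.
- Anxiety power at 70 per group, change-score SD 6 × √(2 × (1 − 0.72)) = 4.49: about 0.82, close to the stated 0.81.
- Question 1b, Fisher z at n = 100: about 0.81, close to the stated 0.82.

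**The 1% mortality.** The article gives no survival distribution, so medians and curves are assumed. Exponential: 1 − 2^(−1.85/m). Rising hazard (Weibull, shape 2): 1 − 2^(−(1.85/m)²).

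| Assumed median m | Dead by 8 weeks, exponential | Dead by 8 weeks, rising hazard |
|---|---|---|
| 6 months | 19% | 6% |
| 9 months | 13% | 3% |
| 12 months | 10% | 1.6% |
| 24 months | 5% | 0.4% |

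A death rate of 1% corresponds to a median of about 127 months under the exponential curve, but only about 15 months under the rising hazard.

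**Effect of the missing terms.** Let u be the share of consented patients not randomized and d the share dead or without data at t3. The article gives neither, so these values are illustrations. Complete cases = 246 × 0.70 × (1 − u)(1 − d); approach number = 170/[0.70 × (1 − u)(1 − d)]; decision-aid arm = 172.2 × (1 − u) × 100/170.

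| u, d | Complete at t3 if 246 kept | Approached for 170 complete | Randomized to decision aid |
|---|---|---|---|
| 0%, 5% | 164 | 256 | 101 |
| 10%, 10% | 139 | 300 | 91 |
| 20%, 10% | 124 | 338 | 81 |
| 20%, 20% | 110 | 380 | 81 |

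**Power and precision at the two middle rows,** with complete cases split 100:70. The ANCOVA SD is 6 × √(1 − 0.72²) = 4.16.

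| | 170 complete, 100 in decision-aid arm | u = 10%, d = 10% | u = 20%, d = 10% |
|---|---|---|---|
| Anxiety, ANCOVA, r = 0.72 | 0.92 | 0.86 | 0.82 |
| Anxiety, change score | 0.88 | 0.81 | 0.76 |
| Question 1b, r = 0.28 | 0.81 | 0.77 | 0.72 |
| Question 1a, Wilson interval at 80% | 71-87% | 71-87% | 70-87% |

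**The case against.** The strongest defence is that the arithmetic is exact and the practical damage limited. Both points stand. Anxiety power was computed for 70 per group while 100 and 70 are planned, and the Statistical Analysis section specifies analysis of covariance, which is more efficient than the change score that best reproduces the stated power. That slack absorbs moderate loss. Information desire is recorded at the interview, so deaths and non-return at t3 leave questions 1a, 1b and 2 untouched; only losses before randomization affect them.

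A reader might infer that the survival scale contradicts the 1%. It does not. The lowest category starts at three months, beyond t3 at eight weeks; the spread of patients over the categories is not given; and the top category is open-ended. Nor does 1% require a median of over ten years: that follows only from an exponential curve, and entry requires a Karnofsky score of at least 60, which makes a lower early hazard conceivable.

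A reader might also infer that the anxiety comparison loses its power. At r = 0.72 it does not under moderate loss. The Discussion warns that this correlation may weaken, but it gives no lower value, and that is a separate question.

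Finally, the Discussion mentions non-randomization as a possibility in an argument about envelopes and gives no rate. The size of the loss is therefore unknown. What the defence does not answer is that the sum allows nothing for it.

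**Conclusion.** The concern holds as a gap in the inputs, not an error of calculation. The procedural half is firm and needs no outside data: consent precedes progression and randomization, the article foresees registered patients who are not randomized, follow-up depends on returned questionnaires, and the margin for all of this is about two patients. The mortality half is weaker: 1% is unjustified and looks optimistic, since assumed medians of 6 to 12 months exceed it under both curves tried, but the article does not contradict it.

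Under the two middle loss scenarios, 246 approached gives about 139 or 124 complete cases instead of 170, and about 91 or 81 patients in the decision-aid arm instead of 100. The clearest statistical cost is to question 1b, whose power falls from about 0.81 to 0.77 or 0.72. Question 1a barely changes. Anxiety power stays at or above the stated 0.81 under the planned analysis if r = 0.72, and is 0.81 or 0.76 by change score. All of these sizes depend on assumed loss rates. The figure should be corrected, but the design does not fail because of it.

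**What to change.** - Justify the 1% or replace it with a mortality consistent with the prognosis expected at progression.
- Add explicit terms for consented patients who are not randomized and for t3 non-return.
- Then either restate the approach number as 170/(0.70 × proportion randomized × proportion with t3 data), or keep 246 and report the expected numbers randomized and complete, with the precision and power they give for each question.
- Run recruitment to the stated 100 and 70 randomized, not to a count of patients approached. Say whether 170 means randomized or complete at t3: with 10% lost by t3, 170 randomized gives 170 × 0.90 = 153 complete.

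The cost is revised figures in the Abstract and the Sample size calculation, less favourable than those now stated, and probably more patients to approach. No study procedure or analysis changes.

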### Statistical Analysis

In all the analyses, scale values will be calculated only if at least half of the items are available, by imputing the mean of the available items. Question 1a about the information desire will be answered by calculating the desire rate for prognostic information with a 95% confidence interval. For question 1b, which factors determine information desire, patients will be grouped according to information desire, ranging from 0 (no information desired) to 3 (information on serious adverse events, tumour response, and survival desired). Then comparisons between these four groups will be made. For categorical variables, the Chi-square test will be used. Continuous data will also be analyzed using the Chi-Square test, after a median-split subdivision into two categories. The HADS scores will be divided by use of a clinical cut-off point of 8 [17,30,31]. Bivariate analyses will be presented with p-value of variables related with information desire at the level of p < 0.2. Finally, these variables will be entered simultaneously in a regression model.

For question 2, agreement between the substitute judgment of the oncologist and the patient information desire is determined. Agreement can arise from chance; a measure correcting for chance agreement is the κ statistic, ranging from 0 to 1. A κ of 0.2, 0.5, and 0.8 indicates poor, moderate, and good agreement, respectively [32,33]. In bivariate and multivariate analyses, associations will be sought between agreement and patient variables (sociodemographic, medical, psychological, knowledge and information). Dichotomized variables associated with agreement at a level of p < 0.2 will be entered simultaneously in a regression model.

Question 3, which addresses the effect of the introduction of decision support compared to usual care on patient well-being, will be answered by comparing the intervention group with the usual care group. Analyses of covariance corrected for differences at baseline are used to test the effect of the intervention. For group comparisons at a single point in time, a t test will be performed for continuous variables and the Chi-square test for categorical variables.

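### The 0.82 power stated for question 1b is that of a correlation test; the planned median-split, four-group chi-square test has about 0.41 to 0.46 for continuous predictors

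*Protocol article*

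**What the plan says.** The Sample size calculation states that about 100 intervention-group patients are enough for question 1b to "detect a weak correlation of 0.28 between a predictor and information desire, with α = 0.05 and a power equal to 0.82". For question 2, the oncologist's judgment, it says that "the same analysis applies as for study question 1b".

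The Statistical Analysis section describes the analysis of question 1b in these steps:

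- Outcome: "patients will be grouped according to information desire, ranging from 0 (no information desired) to 3" (all three items desired).
- Comparison: "Then comparisons between these four groups will be made".
- Continuous predictors: "Continuous data will also be analyzed using the Chi-Square test, after a median-split subdivision into two categories". The HADS is the exception and is cut at a referenced clinical value of 8.
- Selection: variables related to information desire at p < 0.2 are reported and then entered together in a regression model. Its type, and the coding of predictors in it, are not stated for question 1b.

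For question 2 the same section plans the κ statistic, followed by association analyses of agreement using dichotomised variables.

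**The concern.** The two sections describe different tests. A correlation test uses the full scale of the predictor and the order of the outcome. The planned test discards both: it reduces the predictor to above or below its median, and it treats the ordered 0–3 score as four unlabelled groups. Each step costs power, so the stated 0.82 cannot be carried over. The issue is not that detail is missing from a condensed article, since both the power and the test are stated.

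At stake is question 1b. Many of the baseline scales in Table 1 are collected as predictors of information desire. The same chi-square test also decides which of them reach the regression model, and a predictor dropped there cannot be recovered later. The Discussion already accepts that the interval between baseline and interview may weaken these associations, so there is little room for further loss.

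**Working it through.** **Inputs from the protocol article.** n about 100, r = 0.28, α = 0.05 and power 0.82 (Sample size calculation). Four groups scored 0–3, median split, chi-square test and p < 0.2 screen (Statistical Analysis).

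**Assumptions.** A two-sided test, a roughly normal predictor, and r = 0.28 as the correlation with the observed 0–3 score. The article does not give the shares of patients in the four groups, so several were tried.

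**1. The plan's figure.** Fisher z: atanh(0.28) × √(100 − 3) = 0.2877 × 9.849 = 2.83. Power = Φ(2.83 − 1.96) = 0.81. The noncentral t gives 0.823. A one-sided test gives 0.88–0.89 and does not match. So 0.82 is the power of a two-sided correlation test on undivided variables.

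**2. The planned test.** Splitting a normal predictor at its median multiplies the correlation by √(2/π) = 0.798, giving 0.28 × 0.798 = 0.223. The noncentrality is 100 × 0.2234² = 4.99.

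- With 1 df (split predictor, order of the outcome kept): power 0.61.
- With 3 df (four unordered groups, as planned): power 0.44, or 0.46 if the noncentrality is taken as n·w²/(1 − w²).

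The median split therefore takes power from about 0.81 to 0.61, and the move to 3 df takes it to about 0.44. With the 3-df test, about 229 patients would be needed for 0.82.

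**3. Dependence on the assumed group shares.** Exact cell probabilities come from a normal latent desire cut into four groups, calibrated so that the score correlation is 0.28, with 40,000 simulated tables each.

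| Shares in groups 0/1/2/3 (%) | Power at 0.05, noncentral χ² | Power at 0.05, simulated | Passing p < 0.2, noncentral χ² | Passing p < 0.2, simulated |
|---|---|---|---|---|
| 25/25/25/25 | 0.45 | 0.45 | 0.72 | 0.72 |
| 10/15/25/50 | 0.46 | 0.45 | 0.72 | 0.72 |
| 5/10/15/70 | 0.46 | 0.44 | 0.72 | 0.73 |
| 5/5/10/80 | 0.46 | 0.43 | 0.73 | 0.74 |
| 2/6/12/80 | 0.45 | 0.42 | 0.72 | 0.73 |

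A separate simulation (10,000 replicates) gave 0.41 for 3/5/12/80 and 0.44 for 10/10/20/60. Spearman's correlation on the same data gave 0.79–0.80.

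**4. At the screen.** For p < 0.2 the noncentral chi-square gives 0.71–0.73 (0.71 from step 2, the rest from the table). Spearman on the undivided predictor passes 93–94%. Lost before the regression: 100 − 73 = 27% to 100 − 71 = 29%, against 6–7%.

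**5. Another reading of 0.28.** If 0.28 is the association with the predictor after splitting, the noncentrality is 100 × 0.28² = 7.84. Power is then 0.64 with 3 df at 0.05, and 0.86 at p < 0.2.

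**6. Cell counts.** Group 3 requires all three items, so the assumed 80% desire for prognostic information is a ceiling for its share. At that ceiling, 20 of 100 patients fill three groups. The smallest group has at most 6, and its expected count per cell after a median split is at most 6/2 = 3. With 3/5/12/80 the expected counts in groups 0, 1 and 2 are 1.5, 2.5 and 6.

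**7. Question 2.** The simulated SD of κ at n = 100 with 80% desire is 0.08–0.12, so the 95% half-width is 1.96 × 0.08 = 0.16 to 1.96 × 0.12 = 0.24, or about ±0.2.

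**The case against.** The strongest reply is that the article never says which correlation it means. It names no test and no sidedness. It does not say whether the predictor is divided, or whether desire is the 0–3 score or a yes/no item. If both were already dichotomised, a 1-df test with an association of 0.28 has power 0.80, close to the stated figure. That is a fair point about the inference, but the plan compares four groups, and under the same reading the four-group test has 0.64. The shortfall is smaller but remains.

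A reader might infer that the trial would miss more than half of the predictors it claims to detect. The documents do not support that. The plan selects at p < 0.2, not 0.05, and about 71–73% of such predictors pass. The 0.41–0.46 is the like-for-like counterpart of the stated 0.82, not the plan's miss rate.

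A reader might also infer that every cell in groups 0–2 is too sparse. That does not follow either: 80% is a ceiling for group 3, no distribution is given, and group 2 can have expected counts above 5 even at the ceiling.

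Two further points stand. The HADS cut-off is prespecified and clinical, not a data-driven split. For question 2, κ equals a correlation (φ) when the two sets of marginals match, so a correlation-based power figure is not unrelated to it.

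Finally, the Abstract presents these factors as being explored, and the 100 patients are independently justified by the confidence interval for question 1a.

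**Conclusion.** The mismatch holds. The 0.82 describes a two-sided correlation test that the Statistical Analysis section does not plan for question 1b. For a roughly normal predictor correlated 0.28 with the 0–3 score, the planned test has power of about 0.41–0.46 at α = 0.05, or about 0.64 if 0.28 already refers to the split predictor. On the main reading, roughly 27–29% of such predictors are lost at the p < 0.2 screen instead of 6–7%. If group 3 is close to its 80% ceiling, the smallest groups also have expected counts below 5, where the chi-square approximation is poor.

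These figures rest on assumed group shares, to which they are not sensitive. They do not cover truly categorical predictors, or the HADS cut at 8, where the loss depends on the share above the cut-off. The question 2 point is secondary: its main analysis is κ, so precision describes its sample size better than a reference to question 1b.

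This should be fixed, but it is not critical. The estimate for question 1a, the randomised anxiety comparison and the number of patients are unaffected.

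**What to change.** For question 1b, keep continuous predictors undivided and relate them to the ordered 0–3 score by Spearman's correlation or a proportional-odds model at the bivariate step. Use the ordinal model, with undivided predictors, at the multivariable step. Keep chi-square or Fisher tests for truly categorical predictors. The HADS cut-off of 8 may stay as a descriptive clinical split.

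If the chi-square plan is kept, restate the power for continuous predictors as about 0.4–0.45 and state the group shares assumed.

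For question 2, replace the reference to question 1b by the expected precision of κ at n = 100, about ±0.2.

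The cost is rewording the analysis paragraph and, for question 2, one sentence of the sample size section. No new patients, data or procedures are needed. The small downside is that results appear as correlations or odds ratios instead of simple two-way percentages.

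### Question 1b tests a long list of median-split predictors in about 100 patients, screened at p < 0.2 with no allowance for multiplicity or selection, so the determinants it reports would be unreliable

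*Protocol article*

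**What the plan says.** The Statistical Analysis section of the protocol article groups patients by an information-desire score from 0 to 3 and compares the four groups. Categorical variables are tested by chi-square. For the rest, "Continuous data will also be analyzed using the Chi-Square test, after a median-split subdivision into two categories", except that HADS scores are cut at 8. Selection follows: "Bivariate analyses will be presented with p-value of variables related with information desire at the level of p < 0.2". The last step is a joint model containing every variable that passed, and the type of regression is not named. For the oncologist's agreement with the patient (question 2) the rule returns: "Dichotomized variables associated with agreement at a level of p < 0.2 will be entered simultaneously in a regression model".

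The Sample size calculation section supports question 1b with a single-predictor statement: "For study question 1b, regarding factors that determine information desire, again about 100 patients will suffice to detect a weak correlation of 0.28". The power claimed for this is 0.82, at a significance level of 0.05. The same section assumes that 80% of patients will want prognostic information.

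The candidates are listed under Procedure, Sociodemographic variables and medical history, and Table 1. No total is given.

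**The concern.** The power statement concerns one correlation tested alone. The analysis tests dozens of predictors, keeps every one that clears a loose threshold, and reads the survivors from one joint model as if they had been chosen in advance. Chance alone should supply several survivors and often a nominally significant one. Splitting continuous scales at the median also discards information that the power figure assumes is used.

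Question 1b is a named research question, and the Discussion says the study will show whether information desire can be predicted and that the results can improve information giving in practice. A false determinant could shape whom clinicians expect to want a prognosis. The issue is a rule that the text states, not detail left to a fuller document.

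**Working it through.** **1. The plan's own power figure.** Two-sided test of one correlation, r = 0.28, n = 100, α = 0.05. Noncentrality = r/√(1−r²) × √n = 0.28/0.96 × 10 = 2.92. The noncentral t with 98 degrees of freedom gives power 0.823 (Fisher z: 0.809). The stated 0.82 is reproduced, for a single test with the predictor unsplit.

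**2. Effect of the median split.** For a normally distributed predictor the split multiplies the correlation by √(2/π) = 0.798, so 0.28 becomes 0.223. Noncentrality = 0.223/√(1−0.223²) × 10 = 2.29, and power is about 0.62. This is at α = 0.05 on one degree of freedom. HADS, cut at 8, is not covered by this figure.

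**3. Number of candidates.** Counted from the measures available before the interview:

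| Group | Number |
|---|---|
| Demographic | 6 |
| Self-reported earlier chemotherapy (benefits, adverse events, time since last course) | 3 |
| Medical history from the inclusion form | 3 |
| Oncologist's survival estimate | 1 |
| Well-being | 5 |
| Coping (adjustment 3, decision style 4, participation preference 1, death avoidance 1) | 9 |
| Information, including numeracy | 3 |
| General subjective knowledge | 1 |
| Quality/quantity of life | 2 |
| **Total** | **33** |

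Counting quality-of-life subscales separately would raise the total; a narrower reading would lower it.

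**4. Expected by chance if no predictor is real.** Passing the screen: 33 × 0.2 = 6.6. Nominal p < 0.05 without any screen: 33 × 0.05 = 1.65. At least one among 33 independent unscreened tests: 1 − 0.95^33 = 0.816; among 20: 1 − 0.95^20 = 0.642.

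**5. The planned procedure, simulated.** n = 100, no true predictor, median-split predictors in blocks of 5, screen at p < 0.2, all survivors in one model, final threshold 0.05, 2000 runs per setting. Scores 0/1/2/3 are assumed to occur in 5/5/10/80%. The correlation ρ is the latent one within blocks.

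| Candidates | Screen and model | ρ | Mean entering | At least one p < 0.05 |
|---|---|---|---|---|
| 33 | four groups, linear on 0–3 | 0 | 6.8 | 71% |
| 33 | four groups, linear on 0–3 | 0.3 | 6.7 | 69% |
| 33 | four groups, linear on 0–3 | 0.5 | 6.7 | 61% |
| 33 | binary, logistic | 0 | 6.4 | 74% |
| 33 | binary, logistic | 0.5 | 6.5 | 62% |
| 25 | four groups, linear | 0.3 | 5.2 | 58% |
| 20 | four groups, linear | 0.3 | 4.1 | 53% |
| 20 | four groups, linear | 0.5 | 4.1 | 45% |

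A second assumed split (2/3/15/80%) with 33 candidates and ρ = 0.3 gives 65%. Varying the correlation pattern further gives overall ranges of roughly 58–75% with 33 candidates and 45–60% with 20.

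**6. What the screen does.** With 33 independent candidates, screen plus linear model gives 71%, below the 82% for unscreened tests. The mean number of false findings is 1.25, or 1.25/33 = 3.8% per candidate. So the screen does not raise the chance of a false finding. Among variables that enter, however, 1.25/6.79 = 18% have p < 0.05, where a pre-chosen null variable should show 5%. For the bivariate p-values the figure is 0.05/0.20 = 25%. That is the over-optimism caused by selection.

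**7. Events per variable.** At 80% desire about 20 of 100 patients do not want prognosis, and 20/6.6 ≈ 3. This applies only if the regression is on binary desire for survival information.

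**The case against.** The strongest reply has four parts.

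- **Status of the question.** The Abstract speaks of exploring factors, and the Sample size calculation makes whether patients want to be informed the primary question. Neither that estimate nor the randomised anxiety comparison is touched. This stands, and it limits the severity. But question 1b is still phrased as asking which factors determine desire, and the Statistical Analysis section attaches no exploratory label.
- **The complete null is unrealistic.** The Background reports known links with age, education, time since diagnosis and disease stage. True, so the percentages describe a reference case rather than a forecast. If some predictors are real, the remaining noise variables are still exposed.
- **The p < 0.2 filter is not the culprit.** This is correct. A reader might infer that the filter creates the false findings and that removing it would cure them. Step 6 shows otherwise: removing it while still testing 33 variables would leave the problem in place.
- **The outcome is the 0–3 score.** A reader might infer a logistic model overfitted at about 3 events per variable. The article names no regression type, and on a linear model of the score that figure does not apply. The false-positive rate is much the same either way.

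A reader might also carry the percentages over to question 2. The article gives no expected agreement rate, so only the reuse of the rule can be stated there.

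**Conclusion.** The concern holds in this form: the stated procedure for question 1b gives unreliable determinants, mainly because a long candidate list is tested without a multiplicity allowance, and secondarily because selection is ignored in the final p-values and coefficients. The sizes are those in steps 4 to 6. They rest on a candidate count taken from the lists, no true predictor, a final threshold of 0.05 (stated only for the power calculation), and assumed score splits and correlations. A flat statement that the analysis will usually yield spurious factors goes too far: with about 20 correlated candidates the chance is near one half.

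Separately, the stated power of 0.82 does not describe the planned test; about 0.62 is closer for a normally distributed predictor split at its median. The primary estimate and the randomised comparison are unaffected.

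**What to change.** Before any data are seen:

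- Name about 6 to 8 predictors for question 1b, for example age, education and time since diagnosis from the Background, plus a few key scales.
- Keep continuous predictors and HADS on their original scales.
- Enter the whole list together, without the p < 0.2 filter, in an ordinal or linear model of the 0–3 score. If desire for survival information is preferred as the outcome, use a penalised logistic model and state that the outcome has changed.
- Report estimates with confidence intervals and allow for multiplicity within the list. A short list alone is not enough: 1 − 0.95^6 = 26% and 1 − 0.95^8 = 34% for at least one false finding if the tests are independent.
- Label all other associations, and the question 2 agreement model, as exploratory.

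This changes analysis wording only; no extra patients or data are needed. The cost is that fewer factors are formally tested and the list must be agreed in advance.
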